#### Clinical directors and managers

We will provide information about the study to clinical directors and managers at baseline and aim to recruit all relevant managers at each site for interviews to be conducted upon completion of the study.

### Study integrity

Multisite ethical approval for both sites involved in recruitment of participants into this study has been obtained from the Human Research Ethics Committee of RBWH (HREC/13/QRBW/94, dated 24 April 2013), and administrative ethical approval has been obtained from the human research ethics committees of the University of Queensland (Medical Research Ethics Committee approval 2013000654, dated 24 May 2013) and the Queensland University of Technology (approval 1300000640, dated 11 October 2013). The study will be conducted in accordance with the ethical standards of the responsible institutional human ethics committees and the Declaration of Helsinki (1983 revision). The study will be conducted in adherence to the CONSORT (Consolidated Standards of Reporting Trials) statement on randomised trials [35] and will be carried out concurrently at the two cancer services. Every consecutive patient attending the outpatient H&N cancer clinic at each cancer service will be screened for eligibility by a trained research assistant and enrolled if eligible and consenting. Careful documentation of outpatient attendance, subsequent enrolments and consent interviews will ensure that no patient is “selected” for inclusion or exclusion from the study.

The central project manager will allocate patients to one of the three study arms using a computer-generated list of random numbers. The manager will notify trained nurses, who will then contact those patients who have been randomised to receive the intervention. Fidelity to the treatment protocol will be ensured through rigorous training of nurses by means of a standardised manual, and skills development will be facilitated by JT, PY and [name]. In addition, nurses will participate in fortnightly supervision whilst delivering the interventions. At least one session conducted by a nurse each month will be audio-recorded to assess compliance with the study protocol and to provide feedback to the nurse. The central project manager or his or her delegate will forward copies of the resource guide “Facing the Future: Living with Confidence after Treatment for Head and Neck Cancer” directly to patients randomised to the information-only arm of the study.

Research staff involved in pre- and postintervention assessments will be blinded to the allocation status of the patient, as will clinical staff. If group allocation is inadvertently revealed to research staff by patients during follow-up assessments, this information will be recorded and analysis will be undertaken to assess for any effects.

No participating oncology nurses will be randomised. All will receive the training and will have an opportunity to deliver the HNCP to patients who have been randomised to receive the intervention.

### Measures

#### Oncology nurses

At recruitment, participating nurses will be asked to provide demographic information and details regarding their clinical experience and specific training in psychooncology. Upon conclusion of the study, the nurses will be asked to participate in a semistructured interview designed to elicit their perceptions of participation in the study as well as enablers and barriers to implementation of this model of care in routine clinical practice.

#### Patient measures

Patient measures will be completed at baseline and at 3-month and 6-month follow-up appointments.

### Clinical and demographic characteristics

At baseline, structured templates will be used to record age, marital status, education, tumour site, location and extent of metastases and anticancer and supportive therapies. Changes in clinical status and subsequent receipt of any anticancer treatment (surgery, chemotherapy and/or radiotherapy) and supportive treatments will be recorded at other time points to enable comparison of the intervention (the HNCP) with the information-only and usual-care groups on key clinical and treatment variables that may influence the effectiveness of the intervention or the outcomes of interest in this study.

### Primary outcome

QoL will be assessed using the FACT–H&N instrument [33]. The original FACT–General was developed and validated more than 10 years ago [36] and has been used in hundreds of studies worldwide. It is a self-report instrument consisting of 27 core items designed to assess function in 4 domains: (1) physical well-being, (2) social/family, (3) emotional well-being and (4) functional well-being. The FACT–H&N instrument includes an additional 12 items used to assess H&N cancer–related symptoms, which capture the unique concerns of this patient population that are not obtained with more generic measures [33]. It has been demonstrated to be a reliable and valid measure in this patient population [37]. Items are rated on a 0 to 4 Likert scale, then combined to produce subscale scores for each domain as well as a global QoL score.

### Secondary outcomes

#### Self-efficacy

The Cancer Behaviour Inventory version 2.0 [38] is a measure of self-efficacy for coping with cancer and includes a stress management scale. It consists of 33 items that are used to measure function in seven domains: (1) maintaining activity and independence, (2) seeking and understanding medical information, (3) managing stress, (4) coping with treatment-related side effects, (5) accepting cancer and maintaining a positive attitude, (6) regulating affect and (7) seeking support. This instrument is considered to be reliable and valid as well as sensitive to change over time [38].

#### Mood

The Hospital Anxiety and Depression Scale [39] is a 14-item scale that has good reliability and validity. It has been used extensively in studies of cancer patients. Cutoff scores of 22 and above represent severe disorder, and scores less than 8 represent no disorder.

#### Generic quality of life

The European Quality of Life Questionnaire (EuroQol) 5-level version (EQ-5D) [40] is a preference-based utility instrument that will be used for the economic analysis. The EQ-5D has five dimensions covering multiple aspects of QoL. It is a validated and reliable tool for utility measurement in economic studies. An algorithm has recently been developed for Australian populations within economic studies in Australia [41].

### Process measures

At the conclusion of the study, nurses will be asked a structured series of questions designed to assess perceived enablers and barriers to delivery of the HNCP in clinical practice. Similar information will be obtained from medical and nursing directors at the clinics. In addition, upon the completion of the intervention, patients in the intervention group will be asked to respond to a series of questions related to their perceptions of the effectiveness of the intervention sessions and their satisfaction with them. They will also be asked about factors that facilitated or impeded their ability to participate in the intervention and initiate behaviour changes.

### Economic study

The economic study will be undertaken from a health-care provider’s perspective (public and private hospitals) and will involve assessment of (1) intervention resources by identifying, quantifying and valuing resources using standard methods [42] and (2) utilisation and cost of doctor visits and medications for all participants over the course of a 12-month period covering 3 months preintervention, 6 months during the intervention and 3 months postintervention completion.

Investigators will maintain detailed records of direct costs of delivering the intervention (staffing, training, telephone costs, office consumables and printing and production of educational materials) for the duration of the study. Resources will be valued using standardised national fee schedules, salary schedules for personnel and retail prices for other general consumables. To test the occurrence of the medical offset effect as a benefit of the intervention, administrative data on doctor visits and medications will be requested from Medicare Australia records.

### Statistical analyses

Analyses will be conducted using IBM SPSS version 21 software (IBM SPSS, Chicago, IL, USA). Descriptive statistics of patients’ demographic and clinical characteristics at baseline will be generated for each treatment group for the purpose of considering the success of the randomisation. Summary measures at time 1 (baseline), time 2 (3-month follow-up) and time 3 (6-month follow-up) will be calculated as means for continuous variables and as proportions for categorical measures, including 95% confidence intervals. Separate analyses will be conducted for each outcome variable. For continuous variables, the difference between groups in the change in mean scores over time will be evaluated using a generalized linear mixed effects model with all available data controlled for the potential cluster effect of different sites. Otherwise, logistic regression analysis will be conducted. A group-by-time interaction effect will be included in all models. All analyses will be conducted on an intention-to-treat basis.

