## Methods/Design

### Study aims and hypotheses

Our primary aim in this study is to evaluate the effectiveness of a focused intervention (the HNCP) in improving the QoL of H&N cancer survivors. The HNCP will be developed for each patient in collaboration with an oncology nurse who has participated in focused training in developing an individual’s self-management capacity and will receive clinical supervision during the delivery of the intervention.

Our secondary aims in the study are to evaluate (1) the impact of the HNCP on patient self-efficacy, mood and ability to engage in self-management behaviours that promote optimal health and well-being, (2) the cost impact on the health system of using this model of care in routine clinical practice and (3) the feasibility of integration of the HNCP into routine clinical practice, including identification of systems and patient barriers through interviews with participating nurses, nursing and medical directors of clinics, and patients.

We hypothesise that (1) at 6 months following the intervention, patients who receive the HNCP will have significantly improved QoL compared with patients who do not receive the HNCP, (2) the HNCP will be highly acceptable to patients and (3) at 6 months following the intervention, patients who receive the HNCP will be using significantly fewer health-care resources than patients who do not receive the HNCP.

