#### Patients

The patients eligible for this study must have received treatment for H&N cancer at one of the two cancer services. The inclusion criteria are (1) age 18 years or older; (2) completion of a defined treatment protocol for cancer of the tongue; mouth; salivary glands; pharynx; oro-, hypo- nd/or nasopharynx; nasal cavities; middle ear; sinuses; or larynx or completion of a defined treatment protocol for nonmelanoma skin cancers of the head and neck requiring treatment known to cause toxicity (for example, any one or combination of surgery, radiotherapy or chemotherapy); and (3) possess physical, cognitive and mental status enabling participation in the study. Exclusion criteria are (1) inability to speak and read English; (2) currently receiving low-toxicity treatment for H&N cancer (for example, laser therapy alone); (3) the presence of severe mental, cognitive or physical conditions that would limit the patient’s ability to participate in the study or that require regular ongoing specialist treatment; and (4) advanced disease if life expectancy is expected to be less than 6 months. Informed consent to participate will be obtained from all patients recruited into the study.

There is insufficient evidence from other RCTs on which to base calculation of an adequate sample size for assessing a psychosocial intervention for H&N cancer patients. There are also limited published data about meaningful changes in scores on the Functional Assessment of Cancer Therapy–Head and Neck (FACT–H&N) [32], although this QoL instrument is deemed the most appropriate measurement tool for capturing the unique concerns of patients with H&N cancer [33]. Hence, for this preliminary study, the sample size of 40 patients per group (a total of 120 patients) is based on our capacity to enrol and retain patients, and to conduct the interventions and follow-up, within the time frame for which the study is funded [34]. This study is not powered for hypothesis testing, but it will allow us to determine which changes in the QoL measurement are meaningful to patients and will assist us in calculating the sample size for a subsequent, larger, multisite RCT in which a formal economic cost-effectiveness study can be included.

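### Measuring effects on continuous outcomes as a difference in change, with no stated use of the baseline score, gives a valid but less precise 6-month contrast than the same data allow

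*Protocol article*

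**What the plan says.** The Statistical analyses section of the protocol article fixes three things for continuous outcomes.

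- **Effect measure and model:** "the difference between groups in the change in mean scores over time will be evaluated using a generalized linear mixed effects model".
- **Adjustment:** the model is fitted "with all available data controlled for the potential cluster effect of different sites". No other covariate is named.
- **Interaction:** "A group-by-time interaction effect will be included in all models".

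The same section labels baseline as time 1 of three, in its sentence on descriptive summaries. Baseline demographic and clinical characteristics "will be generated for each treatment group for the purpose of considering the success of the randomisation". Nothing is said about the baseline score as a covariate or about a common baseline mean.

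The first hypothesis (Study aims and hypotheses) sets the time point: "at 6 months following the intervention, patients who receive the HNCP will have significantly improved QoL compared with patients who do not receive the HNCP". On size, the Patients section says that "the sample size of 40 patients per group (a total of 120 patients) is based on our capacity to enrol and retain patients", and "This study is not powered for hypothesis testing".

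**The concern.** A model with group, time and their interaction, in which baseline is one of the responses, normally gives every arm its own baseline mean. The 6-month interaction is then the difference between arms in mean change from baseline. In a randomised trial the true baseline means are equal. A model that does not use this subtracts a baseline difference that is pure noise, at full weight, whatever the correlation between visits.

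The number of patients here is set by capacity within the funded period, so precision cannot be bought with more recruitment. Interval width matters for reading the first hypothesis, and it matters for the study's declared purpose of informing the sample size of a larger trial. FACT–H&N, the primary outcome, is affected, and so is every other continuous outcome given the same model.

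**Working it through.** **Inputs from the document.** Three arms of 40 (3 × 40 = 120, which agrees with the stated total); visits at baseline, 3 and 6 months; effect measured as a difference in change; contrast of interest at 6 months. There is no alpha, power, effect size or SD, so there is no power figure to reproduce.

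**Assumptions, not in the document.** The correlation r between baseline and 6 months is taken over the range 0.3 to 0.8. SDs are equal across visits (set to 1), data are complete, and site is ignored.

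**Step 1. What the described model estimates.** In a balanced simulated data set, a random-intercept model with group, time and group-by-time gave a 6-month interaction of -0.21898. The raw difference in mean change was also -0.21898, so the two are the same quantity.

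**Step 2. Variances for two arms of n = 40.**

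- Difference in change: (2/n) × 2(1 - r)
- Baseline-adjusted, or common baseline mean: (2/n) × (1 - r²)
- Ratio: (1 - r²) / [2(1 - r)] = (1 + r)/2

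At r = 0.5 the first is 0.05 × 1.00 = 0.0500 and the second 0.05 × 0.75 = 0.0375. Half-widths are 1.96 × √0.0500 = 0.44 and 1.96 × √0.0375 = 0.38.

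| r | Change variance | Adjusted variance | Ratio | 95% half-width, change (SD) | 95% half-width, adjusted (SD) | Equivalent n per arm (40 / ratio) |
|---|---|---|---|---|---|---|
| 0.3 | 0.0700 | 0.0455 | 0.65 | 0.52 | 0.42 | 61.5 |
| 0.5 | 0.0500 | 0.0375 | 0.75 | 0.44 | 0.38 | 53.3 |
| 0.7 | 0.0300 | 0.0255 | 0.85 | 0.34 | 0.31 | 47.1 |
| 0.8 | 0.0200 | 0.0180 | 0.90 | 0.28 | 0.26 | 44.4 |

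**Step 3. Check.** Generalised least squares for three arms and three visits, with free and then with common baseline means, reproduces these variances under both a compound-symmetric and an autoregressive-type covariance. Over 5,000 simulated trials at r = 0.5, the ratio of baseline-adjusted to change-score variance was 0.747.

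**Step 4. Unequal SDs.** Let k be baseline SD divided by 6-month SD. The ratio becomes (1 - r²) / (k² + 1 - 2rk).

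- r = 0.7, k = 0.8: 0.51 / 0.52 = 0.98, almost no gain.
- r = 0.5, k = 0.8: 0.75 / 0.84 = 0.89.
- r = 0.5, k = 1.2: 0.75 / 1.24 = 0.60, a larger gain than with equal SDs.

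The denominator minus the numerator is (k - r)², which is never negative. So, apart from the small cost of estimating the baseline slope, adjustment never loses precision.

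**The case against.** **The model is inferred.** The article does not list the fixed effects. Baseline is called time 1 in the sentence on descriptive summaries, not in the model sentence. A model with constrained baseline means also estimates a difference in change and also contains a group-by-time interaction, so the printed words are compatible with the remedy. The statistical analysis plan is not shown and may specify it. This stands as a limit: separate baseline means are the standard reading, not a literal statement. It does not dispose of the point, because the article does state the effect measure and does name site alone as adjustment.

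**It is not a question of validity.** A reader might infer that the planned contrast is biased, because a chance baseline difference feeds into it. For 40 v 40, one standard error of baseline difference is √(2/40) = 0.22 SD. At r = 0.5 it moves the change contrast by (1 - 0.5) × 0.22 = 0.11 SD. But that shift is conditional on the imbalance that occurred. Over repeated randomisations it averages to zero and is already reflected in the standard error, so the contrast is unbiased and its interval valid.

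**No power is claimed.** A reader might also infer that the trial misses its power. The document cannot support that, since it declares that it was not powered. Any power figure would rest on an effect size and a correlation from outside the document.

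**The pooled comparison is not fixed.** The first hypothesis could be read as 40 HNCP patients against 80 others, but the Statistical analyses section does not specify this. The variance ratio is the same for either contrast; only the half-widths change.

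**Conclusion.** The point holds as one about efficiency. On the standard reading of the article, the 6-month contrast is a difference in change scores, and it is less precise than one that uses a baseline score already being collected. With equal SDs and complete data the variance reduction is 35% at r = 0.3, 25% at 0.5, 15% at 0.7 and 10% at 0.8. At r = 0.5 the gain is worth about 53 patients per arm instead of 40, and at r = 0.7 about 47.

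No single figure should be quoted as the loss. The correlation is not in the document, and the SD ratio between visits can take the gain close to nil or make it larger than shown. It is not negative. The documents do not support calling the planned analysis biased or invalid, or any stated power wrong.

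**What to change.** State in the analysis section how the baseline score is used, in one of two ways.

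1. **Preferred: constrained baseline means.** Keep all three visits as responses and constrain the baseline mean to be equal across arms. Include site, time and group-by-time with a patient-level unstructured covariance. In practice the group main effect is left out and the interaction is coded only at 3 and 6 months. Like the planned model, this retains all available data.
2. **Alternative: baseline as covariate.** Model the 3- and 6-month scores with baseline score, site, group, time and group-by-time. This drops patients who have no baseline score unless it is imputed.

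Take the 6-month contrast from the chosen model for FACT–H&N, and use the same model for the other continuous outcomes.

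The cost is wording only. Baseline measures are already scheduled, and no patients, visits or instruments are added. The Trial status section reports eight patients recruited, so the change can be made well before any outcome comparison. If the statistical analysis plan already specifies either model, a sentence pointing to it is enough.

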### Interventions

The study design is a prospective randomised controlled trial (RCT) of the HNCP intervention using pre- and postintervention assessments. The study will be conducted in the cancer services of two large tertiary referral centres that provide multidisciplinary care for patients with H&N cancer. Oncology nurses at both centres will be recruited to participate in focused training in order to be able to deliver the HNCP. Once a sufficient number of nurses are trained (approximately 15 nurses in total patients will be recruited. The central project manager will use a computer-generated list of random numbers to allocate recruited patients to one of the three study arms that are described in the subsections below.

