#### Information only

In addition to usual care, patients in this group will receive a copy of “Facing the Future: Living with Confidence after Treatment for Head and Neck Cancer”. The central project manager will forward copies of this resource guide directly to patients randomised to this arm of the study. These patients will not have contact with the trained nurses other than in the course of routine clinical care.

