#### Intervention

Each patient randomised to the intervention arm of the study will receive an individualised HNCP within 1 month of completion of treatment. The HNCP will be developed during a face-to-face supportive and educational session between the patient and a trained nurse. The session will last up to 60 minutes and will be focused on developing the patient’s self-efficacy to manage identified health concerns. During the consultation, the patient and nurse will collaborate to define problems of concern to the patient and develop strategies targeted to address these concerns through practical goal-setting and planning. Information will be provided about symptom management, and strategies to promote behaviour change will also be discussed (for example, in relation to smoking). The HNCP will define follow-up and engagement with health-care systems and sources of community and social support [31]. Patients will also receive a copy of the resource “Facing the Future: Living with Confidence after Treatment for Head and Neck Cancer” and continue to receive usual care. To facilitate consistent, ongoing support, a copy of the HNCP will be sent to the patient’s general practitioner. A summary of the three study arms is presented in Table 2.

**Table 2 T2:** Differences in conditions between the three arms of this study

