### Participants

#### Oncology nurses

Oncology nurses currently working at either cancer service will be eligible to participate if they (1) are registered nurses, (2) have at least 12 months of clinical experience in oncology, (3) are currently engaged in patient contact for at least 6 hours per week, (4) can commit to undertake the necessary training and (5) work in a setting in which they can deliver the intervention (that is, the HNCP). Those nurses who anticipate leaving their current work setting within the next 12 months or taking a period of extended leave during the conduct of the study will not be eligible to participate. Informed consent will be obtained from all nurses recruited to participate in the study.

The recruited oncology nurses will undergo extensive manual-based training to develop advanced knowledge and skills in developing individualised self-management care plans for patients, specifically with respect to the following core concepts: (1) health promotion approaches, (2) assessment of health risk factors, (3) communication skills, (4) assessment of self-management capacity, (5) collaborative care planning, (6) use of peer support, cultural awareness, (7) psychosocial assessment and support, (8) motivational interviewing, (9) collaborative problem definition, (10) goal-setting, (11) action planning and (12) structured problem-solving [24]. After they have worked through the training manual, the nurses will participate in skill development conducted face-to-face by JT, PY and [name]. Decision support tools will provide a framework for the nurses to tailor the HNCP to the specific needs of each patient, and, whilst delivering the intervention, the nurses will participate in fortnightly clinical supervision. Clinical supervision will be conducted in a group format facilitated by JT, PY and [name], who have extensive experience in supervision. During the supervision sessions, participating nurses will present an overview of the HNCPs that they have developed and will be assisted to devise strategies for responding to any challenges they experience. We aim to train 15 oncology nurses so that all will have the opportunity to deliver the HNCP on several occasions, but without posing a burden in terms of their routine clinical roles.

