## Trial status

Fifteen oncology nurses have been recruited and completed training in order to be able to deliver the intervention. Eight patients have been recruited across both sites to date.

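### The outcome model allows for clustering by site only, although the HNCP arm alone is nested within about 15 delivering nurses; HNCP standard errors are somewhat understated if the nurse ICC is above 0

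*Protocol article*

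**What the plan says.** The Statistical analyses section compares groups on change in mean scores over time with a mixed model fitted "with all available data controlled for the potential cluster effect of different sites". It mentions no other source of clustering.

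On sites, the Interventions section says "The study will be conducted in the cancer services of two large tertiary referral centres". In the same section and under Study integrity, individual patients are allocated from a computer-generated random list.

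On delivery, the Intervention subsection says "The HNCP will be developed during a face-to-face supportive and educational session between the patient and a trained nurse". The Oncology nurses subsection says "We aim to train 15 oncology nurses so that all will have the opportunity to deliver the HNCP on several occasions", and Trial status confirms "Fifteen oncology nurses have been recruited and completed training". The Usual care and Information only subsections use the same sentence about their patients: "These patients will not have contact with the trained nurses other than in the course of routine clinical care".

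On size, the Patients subsection sets "the sample size of 40 patients per group (a total of 120 patients") by recruitment capacity and adds: "This study is not powered for hypothesis testing". It also says that the results will help to calculate the sample size of a larger multisite trial.

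**The concern.** This is a partially nested design: one arm is grouped under providers and the other two are not. The protocol treats what the nurse does as an active ingredient. Table 1 lists nurse modelling and persuasion among the techniques, and the Qualitative data section will look for nurse-related factors. The quantitative model has no counterpart to this.

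If patients of the same nurse resemble each other at follow-up, the HNCP arm holds less independent information than 40 patients suggest. A model without a nurse term then understates the standard error of every contrast involving the HNCP. Adjusting for site removes only the between-site part of the nurse variation.

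Two things are at stake: the honesty of the HNCP intervals, and whether the delivering nurse is on record for each patient. Without that record, nurse variation cannot be examined later, either here or when the larger nurse-delivered trial is planned.

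**Working it through.** **Inputs from the protocol.** Three arms of 40, so 3 × 40 = 120, which reproduces the stated total. Fifteen nurses, two sites. There is no alpha, power, effect size or standard deviation to reproduce.

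**Assumed inputs.** The nurse ICC of the outcome as analysed, the spread of caseloads (coefficient of variation, CV) and the number of nurses who actually deliver the HNCP. The protocol gives none of these, so ranges are shown.

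**Formulas.**
- Mean caseload: m = 40/15 = 2.67.
- Design effect, HNCP arm only: DE = 1 + (m(1 + CV²) − 1) × ICC.
- True over naive standard error of the difference, 40 v 40: r = √((DE + 1)/2).
- Actual coverage of a nominal 95% interval: 2Φ(1.96/r) − 1.

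**Worked example** (ICC 0.05, 15 nurses, even caseloads). DE = 1 + 1.67 × 0.05 = 1.083. r = √(2.083/2) = 1.021. Coverage = 2Φ(1.96/1.021) − 1 = 94.5%.

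| Active nurses | CV | ICC | DE | SE larger by | Coverage |
|---|---|---|---|---|---|
| 15 | 0 | 0 | 1.000 | 0% | 95.0% |
| 15 | 0 | 0.01 | 1.017 | 0.4% | 94.9% |
| 15 | 0 | 0.05 | 1.083 | 2.1% | 94.5% |
| 15 | 0 | 0.10 | 1.167 | 4.1% | 94.0% |
| 15 | 0.7 | 0.05 | 1.149 | 3.7% | 94.1% |
| 15 | 0.7 | 0.10 | 1.297 | 7.2% | 93.3% |
| 5 | 0 | 0.05 | 1.350 | 8.4% | 92.9% |
| 5 | 0 | 0.10 | 1.700 | 16.2% | 90.8% |

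**HNCP against the other two arms pooled.** The first hypothesis compares patients who do and do not receive the HNCP, so 40 v 80 is also relevant. Here r = √((DE/40 + 1/80)/(1/40 + 1/80)). With 15 nurses and even caseloads this gives 0.5%, 2.7% and 5.4% at ICC 0.01, 0.05 and 0.10.

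**Check by simulation** (40,000 runs, 40 v 40, t test ignoring nurse). With 15 nurses, type I error is about 5%, 5.3% and 6.0% at ICC 0.01, 0.05 and 0.10. With 5 nurses it is about 5.4%, 7.1% and 9%. This agrees with the formulas.

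**What a nurse term could estimate.** I simulated 10 nurses with 3 patients and 5 with 2, using an analysis-of-variance estimator. The nurse variance estimate is zero or negative in about 41% of trials at ICC 0.05 and about 31% at ICC 0.10. The median 95% interval for the ICC runs from below 0 to about 0.44 and 0.49 respectively.

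**The case against.** The case against giving this much weight is substantial.

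- **Size.** On the protocol's own numbers the caseload is under three patients per nurse, and an SE change of 2% to 4% would rarely alter a reading. This stands.
- **Low ICC.** Common manual-based training, decision support tools, fortnightly group supervision, audio-recorded sessions with feedback, and a care plan developed in a single session all argue for a small nurse effect. They make the low end of the range more plausible but do not make the ICC zero.
- **A preliminary study.** The trial is declared not powered for hypothesis testing. That lowers the consequence of a slightly raised type I error, but it makes the intervals a main product, and the protocol still hypothesises a significant improvement.
- **Little return from the remedy.** With so few patients per nurse the variance estimate will often be zero and the ICC interval wide. This stands and limits the planning value.
- **A condensed article.** Detail of the random-effects structure is commonly left to the full plan. However, the text does address clustering and names only site.

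Three stronger readings are tempting and are not supported.

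1. A reader might infer that the HNCP intervals are too narrow. That holds only if the nurse ICC is above 0, and no ICC is given.
2. A reader might infer a type I error of 6.3% to 7.6% (6.7% to 8.4% for HNCP against both other arms). Those figures follow from the formulas at ICC 0.05 to 0.10, but only with a caseload CV of 1.0. The protocol plans for all 15 nurses to deliver the HNCP several times, which suggests spread caseloads.
3. A reader might infer that site is to be a random effect with a variance estimated from two levels. The text does not say so, and a fixed site effect fits its wording.

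Nor do the other arms have no nurse contact at all. Routine-care contact with the same nurses is allowed, so treating those patients as unclustered is an approximation.

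**Conclusion.** The structural point holds: the stated model allows for clustering by site and omits the nurse clustering that the design creates in the HNCP arm alone. Its consequence is conditional and, on the planned numbers, small: at assumed ICC 0.01 to 0.10 with even caseloads, the table shows coverage no lower than 94.0% for HNCP against one other arm. It becomes material only if delivery falls to a few nurses or the ICC is high, and the protocol neither states nor suggests either. The results assume 40 analysed HNCP patients; fewer would lower the caseload and the effect (at 32 patients over 15 nurses and ICC 0.10, the SE is 2.8% larger). The point is worth making because the correction is cheap and an unrecorded nurse cannot be recovered later, not because this trial's conclusions are at serious risk.

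**What to change.** 1. Record the delivering nurse for each HNCP patient. Trial status reports only eight patients recruited, so this can be nearly complete.
2. State that site enters as a fixed covariate, which is compatible with the present wording.
3. Add a nurse random effect for the HNCP arm's follow-up scores only, since nurses act after baseline. This is a partially nested model with the other arms unclustered and small-sample degrees of freedom. At the least, prespecify it as a sensitivity analysis.
4. State in advance that a zero variance estimate will be reported and the simpler model kept.
5. Report caseloads per nurse and the nurse ICC with its confidence interval. Say plainly that it is imprecise and is one input among others for planning the larger trial.

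The cost is one more recorded field, a few lines of analysis text and slightly wider HNCP intervals. Allocation and sample size do not change.
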